### Ethical Approval

All planned procedures are in accordance with the ethical standards of the institutional and national research committee and with the 1964 Helsinki declaration and its later amendments or comparable ethical standards.

The protocol for the Endoscopy III Project has been approved by the Regional Ethics Committee (H-4-2013-050) and the Danish Data Protection Agency (2007-58-0015/HVH-2013-022).

## Results

We anticipate Part 1 to terminate late August 2016 and Part 2 to terminate late September 2022. The results from Parts 1 and 2 will be presented within 12 to 18 months from termination.

## Discussion

The primary purpose of Part I of the prospective Endoscopy III Project is to validate the RAE model in an asymptomatic population undergoing FIT screening for CRC. While the study is not a direct comparison between FIT and RAE because the population is selected from the Danish CRC Screening Program, and the included participants have either a positive or a negative FIT result, the results may indicate performance status of the RAE model. Another possible outcome is an indication of a complementary performance of the RAE model and FIT. The outcome may lead to future changes in the structure of implemented screening concepts to include a blood test with a possible supplementary feces test or visa-versa, or to offer the participant a choice between the two test modalities.

Most of the included participants in the present study are healthy and asymptomatic but achieved results are not directly referable to a possible screening population because of selection based on positive or negative FIT; hence, a higher or lower prevalence, respectively, of premalignant and malignant large bowel lesions in the two sub-populations is expected compared to the actual prevalence in the Danish population. The benefit of including the two sub-populations in the study leads to the possibility of comparing biomarker levels and/or the presence in high and low prevalence populations.

In Part 2 of the project, blood samples and data from the participants with negative FIT result may lead to information of how to identify those who either have a present or are at risk of developing interval neoplastic lesions. These participants are currently offered a second screening within a scheduled 4-year period according to the Danish CRC Screening Program. Inclusion of blood collection three times within that period may lead to detailed information on the biomarker levels and/or presence compared with the determination at the first screening and the association to risk of having or developing a neoplastic lesion. In addition, the information on velocity of biomarkers in bowel neoplasia may be specifically valuable to establish a basis for future directions of out-patient visits offered to participants at certain risk of developing bowel neoplasia.

At present, FIT is probably the most commonly used screening test for CRC in Europe, and is also in the implementation phase in some American states and Canada, but the test is challenged by low compliance. The compliance to blood sampling in the included participants in the present study is expected to be high due to expectations of a general acceptability in the population to a blood sample compared to a stool sample [11,12]. A previous study has shown compliance to blood sampling among participants with symptoms of CRC referred to colonoscopy of 96% [13]. Participants enrolled in the present Endoscopy III Project have already committed to screening in performing FIT and have accepted a subsequent colonoscopy. Hence, compliance found in the present study may not be directly comparable to the Danish population in general, but can give an indication of compliance to a blood sample in a healthy, screen-relevant population.

The amount of 90 mL blood collected and processed is not necessary for the planned analyses (Table 1). The repository of blood samples may, however, form a solid basis for future projects on new and potentially improved biomarkers of the growth, invasion, and/or dissemination processes of CRC; some of these may either stand alone or be integrated in the RAE model resulting in an improved RAE. The Ethics Committee of the Capital Region of Denmark has approved an amendment to the primary protocol (amendment #43062) to take care of the bio-bank.

The personal information, including information about concurrent diseases collected at the time of inclusion, is registered in the locked database. This provides the opportunity to perform follow-up on the future course of participants diagnosed with CRC or other benign or malignant diseases. The Ethics Committee has approved the follow-up opportunity according to The Danish Health Act §43.1-3, which subsequently is granted by participant signatures at the Consent Declaration. This could lead to hypotheses regarding an association between the analyzed biomarkers in this study and the course/prognosis of CRC. It could also lead to an indication of association between the analyzed biomarkers and presence/course of other malignant diseases; maybe even malignant diseases outside the large bowel [23].

We are aware that the ideal and definite study for validating the RAE would be a study including the background population of Denmark with randomization to outreach FIT or blood collection with subsequent colonoscopy in order to compare the value of the two screening tests. The logistic requirements and cost of such a study would be a major task, and is at present not feasible based on local research opportunities. However, the Endoscopy III Project will contribute to evidence for the use of blood-based biomarkers in the RAE model for CRC screening. The performance of FIT and the blood-based RAE will be compared in both the FIT-positive and FIT-negative cohort with colonoscopy considered as the gold standard. A comparable and/or better performance of the blood-based RAE could ultimately contribute to the argument of planning and financing a comparative, nationwide clinical trial of RAE versus FIT. In recent years, molecular pathological epidemiology has evolved describing premalignant adenomas as a heterogeneous group of various subtypes composed of different combinations of genetic and epigenetic variations in close interaction with non-genetic exposures [26]. Through cellular and extracellular interactions, genetic and epigenetic variants of premalignant adenomas and/or CRC could possibly influence levels of blood-based biological markers in the RAE model. However, collection and pathological evaluation of tissue samples from participants undergoing polypectomy/biopsy of tumor in Part 1 of the study is at present not feasible.

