## Methods

### Part 1

Eligible participants are identified through the Danish CRC Screening Program that is based on an outreach FIT and subsequent offer of colonoscopy to participants with positive test results. The screening program was initiated in March 2014 and is offered to Danish citizens of 50 to 74 years of age. Screening is to be repeated every second year after the initial implementation period of 4 years. The study population consists of two sub-groups, in accordance with the FIT result; FIT-positive participants (hemoglobin [hgb] ≥ 100 ng/mL; OC-Sensor platform) and FIT-negative participants (hgb < 100 ng/mL: OC-Sensor platform).

Participants undergoing subsequent screening colonoscopies at Amager/Hvidovre, Bispebjerg, Herlev, Herning, Hillerød, Holstebro, Horsens, Randers, Silkeborg, and Viborg hospitals will be invited to participate in the project. The result of the positive FIT and booking information for colonoscopy will be forwarded to the screening participants. Simultaneously, an electronic letter with study information and an invitation to attend the Endoscopy III Project will be forwarded to the participants. The inclusion was initiated May 2014 and is planned to terminate by late August 2016. The scheduled number of participating FIT positive participants is set to 8000.

At the day of the colonoscopy an informed consent must be signed by the participants before inclusion into the project; specifically, the study participants also sign that they allow access to health and pathology files according to the Danish Health Act §43,1-3. An interview will be conducted to obtain personal and possible concurrent disease data, followed by blood collection prior to colonoscopy.

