Blood samples of 90 mL will be collected from an antecubital vein with light stasis and subsequently handled and stored according to a validated standard operating procedure including pre-analytical and analytical aspects such as blood sampling, handling, storage, and the effects of freeze/thaw on biomarkers of interest (Multimedia Appendix 1). Specifically, the blood samples for plasma are centrifuged twice to reduce the contaminating effects of leucocyte- and platelet-derived granule proteins. All collection and storage tubes are marked with unique barcodes, which by 8 digits identify the hospital where the sample is collected (2 digits), identification of the subject (4 digits), and identification of the specific tube content (2 digits; serum, plasma or buffy-coat). The Freezer Works PC-based storage handling system is used to track every sample in the -80^o^C freezers, which are electronically surveyed and monitored 24 hours a day, 7 days a week.

Data including findings and interventions at colonoscopy will be registered in a locked Web-based database and continuous audit of the database will be performed ensuring correct data recordings. At the end of the study on-site audit sessions will be performed as well.

The FIT-negative participants are arbitrarily selected from the database of the Danish CRC Screening Program and will be invited to blood collection at the nearest participating hospital. The inclusion started August 2014 and is planned to terminate by late August 2016. A total of 6000 participants will be recruited. The informed consent, data collection, and blood collection, handling, and storage will be carried out according to the procedure for the FIT-positive participants.

The emerging results from the Endoscopy II Project will be used to identify the specific biomarker profile subsequently used in analyzing data for Part 1 of the Endoscopy III Project. The analysis will be carried out as shown in Table 1.

### Part 2

Limitations of FIT screening include suboptimal sensitivity that leads to false negative results, and thereby some participants with CRC or high-risk or medium-risk adenomas (Textbox 1) are not identified.

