Due to the prolonged implementation of FIT screening in Denmark, the period between the first and second screening rounds is estimated to be 4 years; limited colonoscopy capacity will, however, extend the implementation period to about 5 years. Therefore, even low-risk adenoma participants, who far from always are identified by the FIT test, may develop either high-risk/medium-risk adenoma or even early CRC in that prolonged period. Therefore, Part 2 of the Endoscopy III protocol, initiated in March 2016, will include blood samples and data from 30,000 participants screened negative by the FIT testing. The 10 participating hospitals have the capacity to include these participants within 24 to 30 months. Similar to Part 1 FIT-negatives (hgb<100 ng/mL; OC-Sensor platform) the participants are identified and arbitrarily selected from the database of the Danish CRC Screening Program and will be invited to blood collection at the nearest participating hospital. Informed consent, data collection, and blood collection, handling, and storage will be carried out according to the procedure for Part 1 of the project.

At inclusion the participants accept to have blood and data collections after 2 and 4 years, respectively. The third blood and data collection will be approximated to the period just after the second FIT screening testing. All participants will be advised by electronic mail (e-boks in Denmark) 1 month before data and blood collections after 2 and 4 years, respectively.

**Table 1 table1:** Determination of the following biomarkers is in progress or planned in samples from the Endoscopy II Project with national and international academic and biotech laboratories.

Biomarker	Technique or platform
Profile of 8-15 plasma proteins	The Architect Automated platform, Abbott, Chicago, IL, USA
Soluble urokinase plasminogen activator receptor-I (suPAR-I), suPAR-II, suPAR-III, total suPAR	In-house ELISA platforms, Finsen Laboratory, Copenhagen, Denmark
Galectin ligands	In-house ELISA platforms, MD Anderson Cancer Center, Houston, TX, USA
Cathepsins	In-house ELISA platforms, University of Slovenia, Ljubljana, Slovenia
Cell-free DNA	inhouse PCR Platform, Roskilde Hospital, Roskilde, Denmark
Cell-free, tumor-derived DNA	Platform under development, Skejby Hospital, Skejby, Denmark
Nucleosomes	Tecan-based in-house ELISA platforms, Volition, Namur, Belgium
Proteomes	Mass-spectrometry-based platform, primarily tandem LCMS, Applied Proteomics Inc., San Diego, CA, USA

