Metabolomes	Raman Hyperspectral Imaging, ChemImage INC., Pittsburg, PA,USA
YKL-40	Manual commercially available ELISA platform, Herlev Hospital, Herlev, Denmark
Profile of 4 soluble coagulation proteins	Luminex platform, Fred Hutchinson Cancer Research Center, Seattle, WA, USA
Nuclear magnetic resonance (NMR)	NMR profiles, University of Copenhagen, Copenhagen, Denmark
Gas chromatography-mass spectrometry (GC-MS)	GC-MS profiles, University of Copenhagen, Copenhagen, Denmark

Categories of the identified adenomas.Adenoma characteristicsHigh-risk adenomaLesion ≥ 20 mm or≥ 4 lesions orResection by piece-mealMedium-risk adenomaLesion ≥ 10 mm, but ≤ 20 mm or3-4 lesions independent of size orTubulovillous or villous lesion orHigh-grade neoplasiaLow-risk adenoma< 3 lesions (< 10 mm) orTubular lesion orLow-grade neoplasia

### Parts 1 and 2

Intensified follow-up of all included participants will be performed electronically via existing health databases and/or participant-specific health files using the unique 10-digit computerized Central Personal Registration number given to all Danish citizens. Thereby no-one is lost to follow-up. Among the aims are evaluations of the risk of developing intra-bowel as well as extra-bowel neoplasia among those diagnosed with adenomas, other benign bowel lesions, and those without any lesions in relation to the biomarkers determined in the project. It has previously been indicated that blood-based biomarkers may be useful to identify such at risk participants [23]. Specifically, the 30,000 FIT-negative participants will be followed-up according to the same aims to identify those with presence of bowel neoplasia although the FIT result was <100 ng/mL and those at risk of developing interval bowel neoplasia during the 4 to 5 years between the two first screening rounds.

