Based on a number of approved addendums to the protocol the exact FIT hemoglobin concentrations will, among other parameters, be included for everyone participating in the project. Thereby combinations of blood- and feces-based screening platforms may improve the entire screening concept [24]. Among the aims is the ability to evaluate associations between hemoglobin concentrations and CRC or high-risk adenoma, medium risk-adenoma, low-risk adenoma, non-neoplastic bowel lesions or clean colorectum. Thereby, the amount of screen colonoscopies may be reduced significantly and independently of the cut-point hgb level of 100 ng/mL restricted to those who are in urgent need.

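### The promised comparison of FIT and RAE against colonoscopy cannot be made in the FIT-negative cohorts, and in the FIT-positive cohort only with quantitative hemoglobin, conditional on a positive FIT

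*Protocol article*

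**What the plan says.** - **The promise.** The last paragraph of the Discussion says that the performance of FIT and RAE "will be compared in both the FIT-positive and FIT-negative cohort with colonoscopy considered as the gold standard". It adds that comparable or better RAE performance could support planning and financing a nationwide trial of RAE versus FIT.
- **Who gets colonoscopy.** Methods, Part 1 describes a program with a "subsequent offer of colonoscopy to participants with positive test results". The cohorts are split at a hemoglobin of 100 ng/mL.
- **What FIT-negatives get.** In Part 1, "The FIT-negative participants are arbitrarily selected from the database of the Danish CRC Screening Program and will be invited to blood collection". In Part 2, "At inclusion the participants accept to have blood and data collections after 2 and 4 years, respectively". No colonoscopy is named as a study procedure for either group.
- **Follow-up.** Methods, Parts 1 and 2: "Intensified follow-up of all included participants will be performed electronically via existing health databases and/or participant-specific health files". One aim there is to find bowel neoplasia among the 30,000 despite a FIT below the cut-off.
- **Quantitative FIT.** The same section says that exact hemoglobin values will be available for every participant, with an aim to "evaluate associations between hemoglobin concentrations and CRC or high-risk adenoma, medium risk-adenoma, low-risk adenoma, non-neoplastic bowel lesions or clean colorectum". It suggests that screening colonoscopies might then be reduced regardless of the 100 ng/mL cut-off.
- **Disclaimer.** The first paragraph of the Discussion says that "the study is not a direct comparison between FIT and RAE", because participants are selected on their FIT result.
- **Compliance paragraph.** The Discussion also describes enrolled participants as having accepted colonoscopy after FIT, without limiting this to FIT-positives.

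**The concern.** A comparison of two tests needs a reference result in the people compared and a comparator that can vary among them. The promised comparison lacks the first in the FIT-negative cohorts. If FIT means positive or negative, it lacks the second in both cohorts.

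At stake is how the result will be read. The plan wants it to support a national trial. A FIT-versus-RAE result that rests on unverified disease status in FIT-negatives, or on a comparator fixed by the inclusion rule, would reflect how participants were selected more than how the tests perform. The same gap affects the aim of relating hemoglobin to adenoma class and clean colorectum, because below 100 ng/mL those states are not systematically ascertained.

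**Working it through.** **1. The plan's own precision figure.** Statistical Analysis expects 8000 FIT-positives with 450 to 500 CRC cases, and an exact coverage probability above 90% for a half width below 5% on sensitivity. No sensitivity is stated, so I took the worst case, p = 0.5.
- Wald 95% half width, 1.96 × √(p(1−p)/n): 0.046 for n = 450 and 0.044 for n = 500.
- Mean Clopper-Pearson 95% half width: 0.047 and 0.045.
- Exact binomial probability that the estimate lies within 0.05 of the truth: 0.966 and 0.975.

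The figure reproduces. It concerns CRC cases among FIT-positives only, so the present point leaves it untouched.

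**2. Who has a colonoscopy reference by design.**
- FIT-positive: up to 8000.
- FIT-negative: 6000 (Part 1) + 30,000 (Part 2) = 36,000, with none planned at baseline.
- Share without: 36,000 / (8000 + 36,000) = 36,000 / 44,000 = 81.8%.

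**3. Binary FIT within each cohort.** This follows from the inclusion rule, whatever the data.

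| Cohort | Sensitivity | Specificity | Youden (sens + spec − 1) | AUC ((sens + spec)/2) |
|---|---|---|---|---|
| FIT-positive (≥100 ng/mL) | 100% | 0% | 0 | 0.5 |
| FIT-negative (<100 ng/mL) | 0% | 100% | 0 | 0.5 |

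**4. Quantitative FIT.** Hemoglobin varies within each cohort. In FIT-positives, where colonoscopy is offered, its AUC can be estimated and compared with that of RAE. It is truncated at 100 ng/mL, which restricts FIT's range and can favour RAE.

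**5. Can later colonoscopies fill the gap?** A FIT-negative participant reaches colonoscopy through ordinary clinical care or a positive second-round FIT. No colonoscopy triggered by RAE is named. Verification then depends partly on FIT, the comparator itself.
- Part 1: FIT-negatives are enrolled from August 2014 to late August 2016, and results are due 12 to 18 months after late August 2016, so August 2017 to February 2018. Record follow-up at reporting runs from 12 months (last enrolled, earliest report) to 24 + 18 = 42 months (first enrolled, latest report), or about 1 to 3.5 years. Screening began in March 2014 and the first interval is 4 to 5 years, so the second round starts no earlier than about March 2018, after that reporting window.
- Part 2: the third sample is timed just after the second FIT, so some second-round colonoscopies will occur, in those then FIT-positive.

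**6. Statements side by side.** The first paragraph of the Discussion denies a direct comparison and the last paragraph promises one. The compliance paragraph speaks of accepted colonoscopy for enrolled participants generally, while the Methods give FIT-negatives blood and data collection only.

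**The case against.** The strongest reply is that the protocol already has most of what is needed. Exact hemoglobin is recorded for everyone, so FIT is not constant and a comparison against colonoscopy is feasible in FIT-positives. Record follow-up covers all participants, and the second FIT round sends some FIT-negatives to colonoscopy. CRC, the primary endpoint, is the outcome best suited to record follow-up. The Discussion admits selection by FIT and calls a randomised study ideal. The disputed text is one sentence there, and Statistical Analysis contains no FIT-versus-RAE accuracy test.

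Much of this stands, and it rules out three stronger readings that a reader might infer:
- *That no comparison is possible in either cohort.* The quantitative hemoglobin data contradict this for FIT-positives.
- *That colon status below 100 ng/mL is never observed.* Verification there is partial, delayed and differential, but it is not absent.
- *That FIT-negatives without colonoscopy will be counted as disease-free.* The documents do not say so. Statistical Analysis uses the 6000 as controls for biomarker levels and compares model results between FIT-negative and FIT-positive samples with a linear model.

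The reply does not rescue the sentence itself. It names both cohorts and colonoscopy as the reference, and the Methods provide no such reference in one of them. Admitting the selection elsewhere makes the contradiction plainer.

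**Conclusion.** The concern holds in a limited form. The stated comparison against colonoscopy cannot be carried out as written in the FIT-negative cohorts, where 36,000 of 44,000 planned participants (82%) have no baseline colonoscopy planned. At the 100 ng/mL cut-off no within-cohort comparison is informative in either cohort. In FIT-positives a comparison with quantitative hemoglobin is possible, conditional on a positive FIT. Below the cut-off, adenoma class, non-neoplastic lesions and clean colorectum lack a systematic reference, while diagnosed CRC can be taken from records.

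A reader might go further and call the primary analysis broken. The documents do not support that: the precision statement rests on the 8000 FIT-positives and reproduces. What is wrong is an affirmative statement about the comparison, together with its conflicts with the Methods and with other parts of the Discussion.

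The conclusion assumes that planned enrolment is reached and that the Methods list all study procedures for FIT-negatives. The 82% refers to baseline colonoscopy as planned, not to eventual verification, whose extent the documents do not give.

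**What to change.** 1. **FIT-positive cohort.** Compare RAE, and RAE plus hemoglobin, with quantitative FIT hemoglobin against colonoscopy-confirmed CRC by paired AUC difference. Label every resulting estimate (sensitivity, specificity and AUC difference) as conditional on FIT ≥100 ng/mL, and state that truncation restricts FIT's range and can favour RAE.
2. **FIT-negative cohorts.** Replace colonoscopy with record-diagnosed CRC within a fixed window after blood draw as the reference. Report RAE yield as the CRC rate in flagged versus unflagged participants. Make no sensitivity or specificity claim for adenomas or clean colorectum.
3. **Methods, Parts 1 and 2.** Limit hemoglobin associations with adenoma class, non-neoplastic lesions and clean colorectum, and the claim of reducing colonoscopies regardless of the cut-off, to ≥100 ng/mL. Below that, keep only associations with record-diagnosed CRC, in line with item 2.
4. **Discussion.** Reconcile the disclaimer of a direct comparison, the remark that participants have accepted colonoscopy, and the promised comparison with one another and with the Methods.

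Hemoglobin values and record follow-up are already planned, so no new data are needed and nothing changes in who is offered colonoscopy. The cost is a narrower stated claim.
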